## Abstract

**Background:**

Beyond survival of nowadays >80%, modern childhood cancer treatment strives to preserve long-term health and quality of life. However, the majority of today’s survivors suffer from short- and long-term adverse effects such as cardiovascular and pulmonary diseases, obesity, osteoporosis, fatigue, depression, and reduced physical fitness and quality of life. Regular exercise can play a major role to mitigate or prevent such late-effects. Despite this, there are no data on the effects of regular exercise in childhood cancer survivors from randomized controlled trials (RCTs). *Primary outcome* of the current RCT is therefore the effect of a 12-months exercise program on a composite cardiovascular disease risk score in childhood cancer survivors. *Secondary outcomes* are single cardiovascular disease risk factors, glycaemic control, bone health, body composition, physical fitness, physical activity, quality of life, mental health, fatigue and adverse events (safety).

**Methods:**

A total of 150 childhood cancer survivors aged ≥16 years and diagnosed ≥5 years prior to the study are recruited from Swiss paediatric oncology clinics. Following the baseline assessments patients are randomized 1:1 into an intervention and control group. Thereafter, they are seen at month 3, 6 and 12 for follow-up assessments. The intervention group is asked to add ≥2.5 h of intense physical activity/week, including 30 min of strength building and 2 h of aerobic exercises. In addition, they are told to reduce screen time by 25%. Regular consulting by physiotherapists, individual web-based activity diaries, and pedometer devices are used as motivational tools for the intervention group. The control group is asked to keep their physical activity levels constant.

**Discussion:**

The results of this study will show whether a partially supervised exercise intervention can improve cardiovascular disease risk factors, bone health, body composition, physical activity and fitness, fatigue, mental health and quality of life in childhood cancer survivors. If the program will be effective, all relevant information of the SURfit physical activity intervention will be made available to interested clinics that treat and follow-up childhood cancer patients to promote exercise in their patients.

**Trial registration:**

Prospectively registered in clinicaltrials.gov [NCT02730767], registration date: 10.12.2015.

**Electronic supplementary material:**

The online version of this article (10.1186/s12885-017-3801-8) contains supplementary material, which is available to authorized users.

## Background

Thanks to improvements in diagnosis, treatment and supportive care of childhood cancer patients, 5-year survival rates have increased drastically since the 1960s and reached 81% in the last decade in Europe [1, 2], including Switzerland [3]. However, childhood cancer survivors (CCS) are at risk to develop a series of physical or psychological late-effects, either directly as a result of the tumour and the aggressive treatments received, or secondary due to an unfavourable lifestyle [4–6]. The authors of a recent study estimated that 96% of CCS suffer from any chronic health condition and 81% from a serious or life-threatening chronic disease by the age of 45 years [7]. These late-effects shift the focus of modern childhood cancer treatment and research from pure survival to long-term functionality, health and quality of life [8].

Based on evidence from the general population or adult cancer survivors, we can hypothesise that regular physical activity has the potential to decrease the survivors’ risk for late-effects, such as cardiovascular diseases (CVD) [9–11], stroke [11, 12], second cancers [11, 13], obesity [11, 14], dyslipidaemia [15, 16], insulin resistance and diabetes mellitus [11, 17], osteoporosis [18–21], depression [22, 23], and cognitive decline [24, 25]. Despite these encouraging findings on benefits of exercise in various populations, specific studies on physical activity interventions in adult or adolescent survivors of childhood cancer aiming to reduce late-effects and increase physical activity are scarce. Small controlled exercise interventions over 2–4 months have shown beneficial effects on fatigue [26], metabolic risk factors and fitness [27], but to date no randomized controlled studies have been published.

Furthermore, traditional physical activity interventions in any field usually focus on specific types of exercises (such as strength training, tai chi, etc.) and participants are invited several times per week to join exercise sessions [28]. The problem of such a supervised and standardized approach is that the increase in physical activity is often not maintained by individuals after the intervention has ended and does therefore not lead to a sustained change in their behaviour [28, 29]. Our study is novel in applying an individual and motivational feedback-based approach with a personalized exercise counselling and program embedded in each participant’s daily life. Such an intervention may have a higher potential to result in a lasting behaviour change towards an active lifestyle and therefore ameliorate physical and psychological late-effects.

## Methods/design

This study protocol is written in accordance with the SPIRIT guidelines [30] (see the SPIRIT Checklist in Additional file 1).

### Study objectives

The primary objective of the proposed study is to evaluate the effect of a partially supervised and personalized physical activity program on the cardiovascular disease (CVD) risk of adolescent and adult survivors of childhood cancer in a randomized controlled trial. Secondary objectives are to assess the effect of the physical activity program on single CVD risk factors, glycaemic control, bone health, body composition, physical fitness, physical activity, quality of life, mental health, fatigue and adverse events (safety).

### Primary outcome

The primary outcome of the randomized controlled trial (RCT) is defined as the change in a composite CVD risk score [31, 32] from baseline to 12 months in the participants of the intervention group compared to the participants of the control group. The composite score is based on the assumption that a physical activity intervention shall have overall beneficial effects on the cardio-metabolic risk, affecting most if not all components of the metabolic syndrome. We chose a composite CVD risk score because the prevalence of single components of the metabolic syndrome is low in adolescents and young adults. A longitudinal study showed that a clustered score in adolescents predicted metabolic syndrome in adulthood [33] and was sensitive to change by a physical activity intervention in youth [34]. The composite CVD risk score will be calculated by averaging the z-scores based on gender- and age-specific external references of all components of the metabolic syndrome, including waist circumference, blood pressure, homeostatic model assessment insulin resistance [HOMA-IR], inverted high density lipoprotein cholesterol, triglycerides and cardiorespiratory fitness [32, 34–39].

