### Physical fitness

#### Aerobic fitness

The participants complete a continuous incremental cycling test to volitional exhaustion following the step protocol proposed by Godfrey and colleagues [84] in accordance to the international guidelines for exercise testing [85, 86]. Work rate is increased every minute by 20 W with an initial load of 20 W. At each visit, a 12-lead electrocardiogram (ECG, Schiller CS-200, Schiller AG, Baar, Switzerland) at rest is performed to rule out relevant arrhythmias and other pathologies that may pose a risk to the patient during the cycling test and/or intervention. All participants are tested using a calibrated cycle ergometer (Ergospirometrie-System CS-200 and SCHILLER ERG 911S Plus cycle ergometer [SCHILLER AG], Baar, Switzerland) and metabolic cart (LF8 PowerCube®-Ergo Gas-Analysator [Ganshorn Medizin Electronic], Niederlauer, Germany). The metabolic cart is calibrated before each exercise test with two gases of known concentrations. Peak oxygen uptake (VO_2_peak) is determined by the highest VO_2_ averaged over 30s during the test. Peak performance (Wpeak) is defined as the power maintained over the final 1-min stage of the test plus 5 W for each fulfilled 15 s bout of the non-finished stage. Maximal aerobic power and VO_2_peak will be expressed in percent of predicted [87]. Electrocardiography using chest leads and oxygen saturation measured at the finger (Masimo SET-Monitor Radical-7, [Masimo Corporation], Irvine, USA) are used to monitor the participant throughout the test for safety reasons and to determine maximal heart rate and desaturation under exercise. The test is terminated according to existing guidelines [86]. Blood pressure and Borg Rating of Perceived Exertion (RPE) are assessed at the end of each stage [88, 89]. In addition, heart rate, blood pressure and Borg RPE are assessed 1, 2, and 3 min post exercise to assess recovery as a marker of physical fitness [90].

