#### Sample size

A study by Kriemler and colleagues using the same CVD risk score showed a reduction in the z-score by 14% after a 1-year physical activity intervention in children and adolescents [34]. Our population is older with a history of cancer, intensive treatments and long hospitalisations. We therefore expect higher CVD risk in this population at baseline and even greater changes after an intervention. To be conservative, this study is powered to detect a difference between the intervention and control group of 15% (no change in the control group and 15% change in the intervention group) after the 1-year intervention. For a power of 0.80 and a two-sided type 1 error probability of 0.05, 60 survivors with complete data are required in each study arm. Assuming that 20% of participants will dropout or have missing data, 75 survivors have to be recruited in each arm. From the Swiss Childhood Cancer Registry we identified 4241 eligible 5-year survivors of whom about 1500 were diagnosed and treated in one of the three Swiss Paediatric Oncology Group (SPOG) clinics of initial recruitment (Basel, Lucerne, and Zurich) [3]. Therefore, with an expected participation rate of 20% of the survivors contacted and invited, we will reach a sufficient sample size.

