#### Data analysis

Descriptive statistics will be used for clinical, sociodemographic and prognostic variables measured at baseline (stratified by intervention and control group). We will use frequencies and proportions with 95% confidence intervals (CI) for categorical variables and mean with ±SD or 95% CI (or median and range) for continuous variables. Descriptive analysis of baseline characteristics will be performed as soon as the baseline assessments are completed for all participants. This cross-sectional analysis will inform about the comparability of the treatment groups and the need for adjustment of between treatment group comparisons. Furthermore, baseline assessments will provide important results about characteristics, health behaviours and health status of long-term CCS in Switzerland. We will also compare the distribution of baseline sociodemographic characteristics to the Swiss Childhood Cancer Registry, to estimate the representativeness of our sample.

The primary analysis will be conducted as intention-to-treat analysis (ITT) for the primary outcome (change in composite CVD score from T0 to T12). All participants will be analysed in the group where they were originally allocated and missing data will be imputed by means of last observation carried forward (LOCF) [134]. LOCF is an appropriate procedure in this setting because it will lead to more conservative effect estimates (i.e. towards the null), because lost to follow-up is more likely to occur in the intervention group (because of an intensive and time-consuming programme) which is the group expected to change (improve). Attempt will be done to follow up all randomised participants, even if they withdraw from the allocated treatment. If the parameters of the composite CVD risk score are skewed, they will be transformed to reach normal distribution for calculating the z-scores.

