The secondary analyses include several steps: *First*, we will do the same ITT analysis with appropriate means of imputation of missing data for all the secondary outcomes. *Second*, we will perform sensitivity analysis on the primary and all secondary outcomes, including, a) complete data (complete case analysis), i.e. observations with missing information on relevant variables will be dismissed; b) analysis of intermediate effects after 3 and 6 months of intervention; c) dose-response analysis based on the actual physical activities (min of vigorous physical activities per week) or physical performance (VO_2_peak) during the period of interest, independent of the group allocation; and, d) per protocol analysis.

Per protocol analysis will include several analyses based on the actual “treatment” that the participants adhered to (independent of group allocation), first based on the reported compliance and second based on the assumed compliance. In the first analysis based on the *reported compliance*, the following participants will be analysed as being in the “intervention group”: participants randomized into the intervention group who reported in the web-diary to have reached at least 2/3 of the target physical activity (addition of 100 min of moderate to vigorous physical activities [MVPA]); and, participants who were randomized to the control group but reported in the physical activity questionnaires to have increased their physical activity level by more than 30 min of extra MVPA per week during the period of interest. The rest of the participants will be analysed as being a “control”. The second analysis of *reported compliance* will include only the participants sufficiently compliant with the protocol that they were allocated to. It will include those randomized into the intervention group who completed at least 2/3 of training volume (e.g. the addition of 100 min per week of vigorous PA) and compare them to those randomized into the control group with no more than 30 min of extra vigorous PA per week than at baseline during the period of interest.

The analysis on the *assumed compliance* will be done according to the analyses of the reported compliance but with participants being defined as compliant if they reach an increase of ≥5% in VO2peak and/or ≥10% in the ventilatory anaerobic threshold from baseline [135].

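### The written definition of the primary composite score reverses only HDL cholesterol, so a gain in cardiorespiratory fitness would count as added cardiovascular risk

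*Protocol article*

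**What the plan says.** The protocol article, Primary outcome, says of the score: "The composite CVD risk score will be calculated by averaging the z-scores based on gender- and age-specific external references". Six components follow: waist circumference, blood pressure, HOMA-IR, and then "inverted high density lipoprotein cholesterol, triglycerides and cardiorespiratory fitness". No other section of the article adds to or changes the sign of any component.

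Three other places fix the directions:

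- **The score.** The Sample size section says that an earlier trial with the same score "showed a reduction in the z-score by 14% after a 1-year physical activity intervention in children and adolescents", and presents this as the favourable result. Lower is better.
- **The fitness measure.** Under Aerobic fitness, VO2peak "is determined by the highest VO_2_ averaged over 30s during the test". Peak power is recorded as well. For both, higher is fitter.
- **The expected response.** In the per-protocol part of Data analysis, participants are classed as compliant on the assumed-compliance definition if they "reach an increase of ≥5% in VO2peak and/or ≥10% in the ventilatory anaerobic threshold from baseline". The programme is expected to raise fitness.

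**The concern.** An average of z-scores is a risk score only if every term points the same way. The definition recognises this for HDL cholesterol, which it reverses, but not for fitness, which is protective in the same sense. Taken literally, the VO2peak response that marks a participant as compliant also moves that participant's primary endpoint in the harmful direction.

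The sentence can be read in two ways that its grammar allows. If *inverted* applies to HDL alone, fitness has the wrong sign. If it applies to everything after it, fitness is right but triglycerides, where higher is worse, have the wrong sign. The valid combination (HDL and fitness reversed, triglycerides between them not) is what the sentence does not say.

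At stake is the primary endpoint. A statistician who follows the text would compute an attenuated effect. One who notices the problem after seeing data would have to choose the sign of a primary-endpoint component at that stage.

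**Working it through.** **1. The plan's own figures.** The Sample size section asks for 60 complete participants per arm at power 0.80 and two-sided 0.05, and 75 per arm after 20% loss.

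- 60 / (1 − 0.20) = 75. This reproduces.
- The 60 cannot be reproduced. The difference is given only as a percentage ("no change in the control group and 15% change in the intervention group"), with no SD and no absolute z-score difference.
- Solving backwards with the normal approximation, 60 per arm implies a standardised difference of √(2/60) × (1.960 + 0.842) = 0.511. This serves below as the effect on a correctly signed score.

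**2. Effect of the sign.** Assumptions: six equally weighted terms, a benefit of *d* SD in each of the five non-fitness components, and a benefit of *k·d* in fitness.

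- All terms in the risk direction: change = −(5 + k)d / 6
- Fitness not reversed: change = −(5 − k)d / 6
- Share of the effect retained: (5 − k) / (5 + k)

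**3. Effect on the SD of the score.** Let all pairs of components, coded as risk, have correlation ρ. The variance of the mean is (6 + 30ρ)/36 with correct signs. With one sign flipped, 20 of the 30 off-diagonal terms stay positive and 10 turn negative, which gives (6 + 10ρ)/36. The SD ratio (flipped / correct) is:

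- ρ = 0: 1.000
- ρ = 0.2: √(8/12) = 0.816
- ρ = 0.4: √(10/18) = 0.745

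The smaller SD gives back part of the lost power.

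**4. Power at 60 per arm.** Power = Φ(0.511 × share retained / SD ratio × √30 − 1.960). For k = 1 and ρ = 0: 0.511 × 0.667 × 5.477 = 1.868, and Φ(1.868 − 1.960) = 0.46.

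| Fitness benefit relative to the others (k) | Share retained | Power, SD held (ρ = 0) | Power, ρ = 0.2 | Power, ρ = 0.4 |
|---|---|---|---|---|
| 0.5 | 4.5/5.5 = 82% | 63% | 80% | 87% |
| 1 | 4/6 = 67% | 46% | 63% | 71% |
| 2 | 3/7 = 43% | 22% | 31% | 36% |

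For k = 1 with the SD held, restoring 80% power would need about 60 × (6/4)² = 135 per arm. If systolic and diastolic pressure enter as separate terms (seven in all), k = 1 retains 5/7 = 71%, and power is 52% with the SD held.

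**The case against.** The strongest reply is that this is a list in prose and not a scoring formula. The article takes over an existing score from cited work, and the Sample size section says that the earlier trial used the same one. The sign convention may be correct in those sources. The intent is also clear from the article itself: it calls the result a risk score, expects activity to benefit most or all components, and treats a rise in VO2peak as the sign of a compliant participant. On this view a word is missing and nothing more.

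Much of this stands. The sources are not at hand, fitness may well be reversed in practice, and nothing shows that any analysis is wrong. It does not clear the text, however. The article does state sign handling, and states it for one of the two components that need it. That is a wrong rule for the primary endpoint, not a detail left to a fuller document.

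The objection also holds on size. The protocol gives no component effects, SDs or correlations. If fitness gains half as much as the other components and these correlate at 0.2 or more, power does not fall (80–87%).

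A reader might also infer a second fault. The z-scores rest on external references, yet Data analysis says: "If the parameters of the composite CVD risk score are skewed, they will be transformed to reach normal distribution for calculating the z-scores". This could look like transformed trial values set against untransformed reference values. The article does not support that. It never states the scale of the references, and transforming in order to compute the z-scores is compatible with references on the transformed scale.

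**Conclusion.** The point holds for the written definition of the primary endpoint: no reading that the sentence's grammar allows puts all six components in the risk direction, and nothing elsewhere in the article corrects it.

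The size is illustrative. Under the equal-weight, six-component assumptions above, 43–82% of the intended effect remains as the fitness benefit runs from twice to half that of the other components. The reference case of equal benefit leaves 67%.

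Two stronger conclusions are tempting and not supported. The first is that the primary effect will be cancelled or reversed. Cancellation needs a fitness effect five times that of the other components (5 − k = 0), reversal needs more, and the protocol gives no component effects from which to expect either. The second is that the planned 60 or 75 per arm is wrong because of the sign. That calculation rests on a percentage difference without an SD and does not use the component signs.

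**What to change.** In the Primary outcome definition, state that the z-scores for HDL cholesterol and for cardiorespiratory fitness (VO2peak) are both multiplied by −1 before averaging, that the triglyceride z-score is not, and that a higher score means higher risk.

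The cost is one sentence, provided that it is fixed before the score is computed. Design, data collection and sample size are unaffected. The external age- and gender-specific references and the rule on skewed components need no change on this account. Replacing some references with the trial's own pooled baseline values would mix internal and external standardisation within one score.

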### Secondary outcomes

Secondary outcomes are differences in change between the intervention and control group from baseline to 6 months for the composite cardiovascular disease risk score, and from baseline to 6 and 12 months for the single CVD risk factors, glycaemic control, bone health, body composition, physical fitness, physical activity, quality of life, mental health, fatigue and adverse events (safety). Additional file 2: Table S1 lists all assessed outcome variables.

### Study design

This study is a single-centre RCT including childhood cancer survivors from various paediatric oncology clinics of Switzerland. Control and intervention arms run parallel (Fig. 1). Assessments are performed at baseline (T0) and after three (T3), six (T6), and 12 (T12) months. The assessments at T0, T6 and T12 comprise of two visits (a and b, respectively) in the study centre, 14 days apart, and T3 of one visit. Randomization is performed after the first visit of T0 (T0a) (Additional file 2: Table S1**,** Fig. 1). A motivational interview for the intervention group is performed at the second visit of T0 (T0b). After the intervention period, controls are offered a similar personalized exercise programme without long-term coaching (see paragraph on physical activity intervention). Eligible participants are contacted, informed and, if consenting, enrolled into the study (see paragraph on recruitment) until we reach the pre-defined number of participants.

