### Physical activity

#### Pedometer

Participants wear a pedometer (Fitbug Air®, Fitbug, London, United Kingdom) between the two visits of T0, T6 and T12, to count number of daily steps (divided into overall steps and aerobic steps) [100]. The steps per day of the preceding 14 days are stored in the device and entered into the REDCap database when the participant returns the device at the second visit.

In addition, participants of the intervention group will wear a pedometer and record their daily steps throughout the entire study period (see paragraph on physical activity intervention).

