#### Accelerometer

Physical activity (PA) is assessed by accelerometer (ActiGraph, Pensacola, Florida, USA) which will be worn on the right hip during at least 7 days between the two visits of T0, T6 and T12. The device measures accelerations of ±6 G. The sample rate of the accelerometer will be set to measure raw signals at 100 Hz. These are then translated into either metabolic energy equivalents of no, light, moderate and vigorous physical activities to estimate the effect on the metabolic outcomes or in cumulative impacts per day for the bone outcomes. Data are included if at least four full days (including at least one weekend day) with a minimum of 10 h are measured [101]. Participants are asked to wear the accelerometer also at night to capture sleeping time. Validity of accelerometer is good with correlation coefficients of 0.65 between accelerometer assessed metabolic energy equivalents and indirect calorimetry [102], and 0.74 between accelerometer impact loading and ground reaction forces by force plates [103]. For metabolic outcomes, overall PA will be expressed as total PA (total counts), average PA in counts/min, as well as time (min/d) sedentary and in light, moderate and vigorous PAs according to proposed, previously published cut-off levels [101, 102, 104]. For bone outcomes, impact loading will be expressed as cumulative impacts per day (n/day) >2, 3, 4, 5 and 6 G, respectively. Less than 100 impact loadings >3.9 G per day were shown to be effective to increase bone mineral density in premenopausal women with higher effects in those with low baseline values [105]. Such a level is reached with jogging, fast running and jumping activities.

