#### Physical activity intervention (intervention group)

Survivors in the intervention group are asked to add at least 2.5 h of intense physical activities per week. These should include 30 min of strength building exercises and 2 h of aerobic exercises per week. Exercise bouts lasting 20 min or longer are counted towards the total weekly training time. This “dose” of physical activity is based on the international recommendations of healthy physical activities from the Centre of Disease Control and Prevention (CDC; www.cdc.gov) [133].

Based on the initial exercise test, general health status and participant’s preferences and motivation, subjects of the intervention group receive a counselling at the second visit of the baseline assessment (T0b; Fig. 1
**,** Additional file 2: Table S1). A standardized approach is used to assess survivors’ preferences with respect to physical activities, identify possible barriers and determine the individual motivation to start specific activities. Based on this assessment, individualized physical activities are defined and implemented into the participant’s daily life. Survivors of the intervention group are also motivated to incorporate activities of moderate intensities into daily life such as walking instead of driving or climbing stairs instead of taking the escalator. Participants are also advised to reduce inactive behaviour such as television viewing, computer games, etc. with the aim of reducing 25% of their actual media time. The motivational interview is performed by one of the project physiotherapists who have been trained prior to the study.

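### The T0 pedometer and accelerometer baseline is recorded after randomisation, so a participant who already knows the arm can alter it

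*Protocol article*

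**What the plan says.** All references are to the protocol article.

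- **Order of events.** Study design: "The assessments at T0, T6 and T12 comprise of two visits (a and b, respectively) in the study centre, 14 days apart". The same section says "Randomization is performed after the first visit of T0 (T0a" and "A motivational interview for the intervention group is performed at the second visit of T0 (T0b". The intervention section agrees that intervention participants "receive a counselling at the second visit of the baseline assessment".
- **Baseline devices.** The Pedometer section has the device worn "between the two visits of T0, T6 and T12, to count number of daily steps", and at the second visit "The steps per day of the preceding 14 days are stored in the device and entered into the REDCap database". The Accelerometer section has that device "worn on the right hip during at least 7 days between the two visits of T0, T6 and T12".
- **The abstract.** Its Methods paragraph has a different order: "Following the baseline assessments patients are randomized 1:1 into an intervention and control group".
- **Use of the data.** Secondary outcomes lists physical activity among the outcomes compared between arms as change from baseline to 6 and 12 months.
- **Blinding.** The Blinding section accepts that participants cannot be blinded.

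**The concern.** A baseline protects a randomised comparison because allocation cannot have influenced it. Here it could have. One arm is asked to add 2.5 hours of intense activity a week and the other to stay as it is. The inclusion criteria require participants to commit in advance to either allocation. A participant who learns the result soon after T0a could start early, or ease off, while the devices are recording what is later called baseline.

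Three uses of the device data would inherit this:

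- The between-arm difference in change, because part of the effect would sit in the baseline.
- The baseline comparison in Data analysis, which is meant to show whether adjustment is needed. A difference caused by allocation would look like chance imbalance.
- Any descriptive check, under Compliance, of whether each arm kept to its aim, if T6 and T12 device activity is compared with T0.

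The abstract adds to the problem, since its readers will take the whole baseline to be pre-randomisation.

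**Working it through.** **Step 1: the timeline.** Setting the sections side by side gives this sequence:

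| Event | Time | Section |
|---|---|---|
| T0a | day 0 | Study design |
| Randomisation | after T0a, exact day not given | Study design |
| Pedometer wear, 14 days of steps stored | T0a to T0b | Pedometer |
| Accelerometer wear, 7 days or more | T0a to T0b | Accelerometer |
| T0b: devices in, motivational interview | day 14 | Study design; Pedometer |

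On the natural reading the whole device baseline follows randomisation. It also ends before counselling begins, so any early change would come from knowing the arm and not from the intervention sessions.

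**Step 2: effect on the change score.** The article states no figure that could be reproduced here, so this is an illustration. Let a_I and a_C be the shifts in weekly activity during the wear window caused by knowing the allocation. Then

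recorded difference in change = true difference − (a_I − a_C).

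Take the target of 2.5 h = 150 min/week as the true difference, a_C = 0 and a_I = x:

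| Assumed x (min/week) | Recorded difference | Share lost, x/150 |
|---|---|---|
| 0 | 150 − 0 = 150 | 0% |
| 15 | 150 − 15 = 135 | 10% |
| 30 | 150 − 30 = 120 | 20% |
| 50 | 150 − 50 = 100 | 33% |

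The values of x are assumptions; the article gives none. If controls eased off (a_C below 0) the loss would be larger. If they also became more active it would be smaller.

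**Step 3: does baseline adjustment help?** The Model selection paragraph allows adjustment for baseline values. With slope b of follow-up on baseline, the adjusted contrast is the follow-up difference minus b times the baseline difference. The part of the baseline difference due to allocation therefore biases the contrast by −b(a_I − a_C). With b between 0 and 1 this is smaller than in Step 2, but it vanishes only if b = 0, that is, if the baseline is not used.

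**Step 4: what else depends on the devices?**

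- The primary score (Primary outcome) averages waist circumference, blood pressure, HOMA-IR, HDL cholesterol, triglycerides and cardiorespiratory fitness. It has no device component.
- The per-protocol rules in Data analysis use the web diary, activity questionnaires, VO2peak and the ventilatory threshold. None names the pedometer or accelerometer.

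**The case against.** The strongest reply is that the bias depends on something the article does not state. It gives neither the day of randomisation within the fortnight nor the moment participants learn the result. An external collaborator runs the allocation, and the supplementary schedule and Fig. 1 are not shown. If disclosure waits until T0b, the device baseline is clean. This stands: the order of events is documented, but the bias is only a risk.

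A second reply is that the abstract is merely loose and Study design is the operative text. That is fair as to which text governs, but the operative text is the one that puts device wear after randomisation.

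A reader might also infer three stronger points that the document does not support:

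- **Distorted compliance cut-offs.** One might argue that a participant truly adding 120 min would be recorded at 120 − 30 = 90 and miss the 100-min threshold. That threshold is read from the web diary, not from device change. The limit of 30 extra minutes for controls concerns activity above baseline, and the first per-protocol analysis takes it from questionnaires. The exclusion criteria, assessed at T0a, include reported vigorous activity, which suggests that at least this report precedes randomisation.
- **A biased primary outcome.** The score contains no device activity. The exclusion for arrhythmia under exercise, also assessed at T0a, suggests that the exercise test is done there too.
- **Early randomisation serves no purpose.** Only the intervention arm has an interview with a trained physiotherapist at T0b, and knowing the arm beforehand plausibly helps to schedule it.

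**Conclusion.** The point holds for device-measured physical activity. Its T0 values are collected after randomisation, in unblinded participants, for an outcome analysed as change from baseline, and the abstract states a different order.

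Whether bias follows depends on participants knowing their arm during wear, which the article leaves open. If they do, the unadjusted change would lose between 0% and 33% of the 150-min target for an assumed early uptake of 0 to 50 min/week, taking controls as unchanged. Baseline adjustment would not reliably repair this. Comparing T6 or T12 device levels without using the baseline would avoid this source of bias.

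No effect is shown on the primary outcome or on the per-protocol compliance cut-offs. The change is worth making because it is cheap and removes an avoidable risk to one secondary outcome; the point does not call the main result into question.

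**What to change.** 1. Run the web-based minimisation at T0b, after the devices are returned and any remaining baseline assessments are done, immediately before the motivational interview. Alternatively, keep randomisation where it is and state that allocation is not disclosed to participants until that same point.
2. Align the abstract and the Study design section so that both give the same order and both say when participants learn their arm.

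The cost is a short procedural amendment. Under the first option the allocation service must be available on T0b days, and the physiotherapist interview must be scheduled without knowing the arm in advance. Under the second option whoever schedules the interview could still know the arm, provided the participant does not. Sample size, the assessments and the primary analysis are unchanged.
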